### Data collection

The following data will be collected from all patients: name, sex, age, race,
height, weight, hospital identification number, date of birth, etiological
diagnostic indicator of transplantation, pretransplantation Model for End-stage
Liver Disease (MELD) score, origin before transplantation (ICU, ward or home),
comorbidities (diabetes mellitus, heart failure, arterial hypertension,
nondialytic chronic renal failure, active cancer, previous stroke or transient
ischemic attack or immunosuppressive therapy in the last 30 days before
surgery), preoperative creatinine, donor risk index (DRI) and use of nephrotoxic
drugs in the week before transplantation.

The following intraoperative data will also be collected: anesthesia time, total
and cold ischemia time of the liver graft, presence of ischemia‒reperfusion
syndrome, time of admission to the ICU, use of blood products, antibiotic
prophylaxis, initial value of arterial lactate, peak arterial lactate, final
value of arterial lactate, use of basiliximab, use of fluids, type of fluids,
episodes of intraoperative hypotension and loss of fluids.

The following postoperative data will also be collected: length of hospital stay
after transplantation; length of stay in the ICU; time of mechanical
ventilation; duration of vasopressor use and maximum vasopressor dose; need for
renal replacement therapy; need for postoperative transfusion; primary graft
dysfunction; secondary graft dysfunction; need for retransplantation; surgical
site infection; Sequential Organ Failure Assessment (SOFA) score on admission to
the ICU; D1, D3 and D7; daily creatinine, to evaluate the presence of acute
kidney failure (AKI) in the first 28 days after transplantation or until
hospital outcome if this occurs before the described period; admission and
48-hour urinary NGAL; presence of surgical site infection in the first 7 days
after transplantation; arrhythmias requiring chemical or electrical treatment in
the first 7 days after transplantation; diagnosis of acute coronary syndrome in
the first 7 days after transplantation; volume of crystalloids infused in the
first 24 hours after surgery; volume of colloids infused in the first 24 hours
after surgery; diuresis in the first 24 hours after surgery; drainage output in
the first 24 hours after surgery; presence of major bleeding in the first 24
hours after surgery; need for transfusion in the first 24 hours after surgery;

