### Statistical analysis

The analyses will be performed according to the “intention-to-treat” principle;
all randomized patients will be included in the analysis according to the
treatment group to which they were randomly assigned. Summary statistics per
group, with treatment effects, 95% confidence intervals and p values, will be
presented for the primary and secondary outcomes. Continuous variables will be
tested for normality using the Shapiro‒Wilk test after graphic analysis by
histogram. Parametric continuous variables between two groups will be compared
with the unpaired *t* test and within the same group with the
paired *t* test. If analysis among more than two groups is
required, analysis of variance (ANOVA) will be used. Nonparametric continuous
variables will be evaluated using the Wilcoxon test or the Mann‒Whitney U test
between two groups and the Kruskal‒Wallis test between three or more groups.
Categorical variables will be evaluated using the chi-square test or Fisher’s
exact test, as appropriate. P values < 0.05 will be considered statistically
significant. The outcomes of hospitalization-free days or renal dysfunction over
time will be calculated based on the 7- and 28-day follow-up, respectively,
using Cox regression models. The calculations of survival curves will be
performed with the Kaplan‒Meier method. For the statistical analysis of
outcomes, the results will be adjusted for previous renal function, and logistic
regression will be used to adjust for other confounding factors that generate
inconsistency in the baseline that were not corrected by the randomization of
the study (use of nephrotoxic drugs, maximum tacrolimus level in the first week,
intraoperative fluid balance and intraoperative major bleeding). No statistical
adjustments will be provided for multiple comparisons in the case of secondary
outcomes, and therefore, we suggest that these be interpreted as exploratory
analyses.

The existence of missing data will be described in the publication and managed
with simple exclusion from the analysis. For this study, no interim analyses are
foreseen.

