## APPENDIX 1 DEFINITIONS OF OUTCOMES

**Protocol:** Comparison between different mean arterial pressure
targets in patients undergoing liver transplantation in an open-label,
controlled, single-center, randomized clinical trial.

□ **Acute renal dysfunction**

Only patients with an increase in serum creatinine by 1.5 times the baseline
value (last value prior to transplantation) will be considered to have renal
dysfunction according to the adaptation of the KDIGO criterion referenced in the
main text. For this, the diuresis criterion was ignored, as it can be difficult
to interpret the real meaning of these data in the postoperative period and in
cirrhotic patients. An increase of 1.5 times was used instead of the criterion
of an increase of 0.3mg/dL because the calculated sample was based on the
criterion of 1.5 times the baseline creatinine.^(1)^

□ **Death within 28 days**

Death within the first 28 days after liver transplantation.

□ **Retransplantation in 28 days**

Conduction of a new liver transplantation within the first 28 days after the
initial transplantation.

□ **Renal replacement therapy in 7 days**

Administration of renal replacement therapy in the first 28 days after liver
transplantation by any modality, prescribed by a specialist team of the
institution itself, based on the classic indications (refractory hyperkalemia,
refractory hypervolemia, refractory acidosis, refractory hypernatremia or
uremia). Patients undergoing renal replacement therapy for ammonia clearance
will not be considered.

□ **Surgical site infection**

Infection at the site of the surgical incision that appears to be related to the
surgical procedure, manifesting as purulent secretion through a drain placed in
the incision of the organ/cavity; organisms isolated from a positive culture of
secretions or tissue of the organ/cavity obtained aseptically; presence of
abscess or other evidence of infection, involving the organ/ cavity, identified
in direct examination, during a new surgery, or through histocytopathological
examination or imaging, which results in surgical approach and/or initiation of
a new regimen of antibiotic therapy, as indicated together by the surgical and
infectious diseases teams.

□ **Days alive and free of renal dysfunction in 7 days**

Number of days during the first 7 postoperative days that the patient was alive
and did not meet the criteria for renal dysfunction consistent with the primary
outcome

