□ **Acute renal dysfunction according to urinary NGAL assessment**

Number of days during the first 7 postoperative days that the patient was alive
and did not meet the following criteria for renal dysfunction: urinary NGAL
value > 150ng/mL. This outcome will be assessed at admission and at 48
hours.^(2)^

□ **Primary graft dysfunction - initial poor function subtype at 7
days**

Development of one of the following laboratory criteria within the first 7 days
after liver transplantation: bilirubin > 10mg/dL on the seventh day after
transplantation; international normalized ratio > 1.6 on the seventh day
after transplantation; alanine aminotransferase or aspartate aminotransferase
> 2,000IU/L in any of the first 7 days after transplantation.^(3)^

□ **Primary allograft dysfunction - primarily nonfunctional subtype at 10
days (Broering)**

Need for retransplantation in the first 10 days after transplantation or death
due to a nonfunctioning graft.^(3)^

□ **Major adverse kidney events in 28 days (MAKE28)**

The incidence of death, need for renal replacement therapy or persistent renal
dysfunction at 28 days after liver transplantation.^(4)^

□ **Days alive and hospitalization-free in 28 days**

Number of days among the first 28 postoperative days in which the patient was
alive and hospitalization-free.

□ **Major postoperative bleeding at 7 days**

Dichotomous outcome of bleeding that indicates, on the same day, the transfusion
of more than two units of packed red blood cells or the need for surgical
intervention indicated in the first 24 postoperative hours.

□ **Transfusion of blood components in 7 days**

Number of blood components transfused in 7 days separated into packed red blood
cells (one unit equal to one bag), fresh frozen plasma (one unit equal to one
bag), fibrinogen concentrate (one unit equal to 1g) and tranexamic acid (one
unit equal to 1g).

□ **Arrhythmias requiring chemical or electrical therapy within 7
days**

Description in the prescription or medical records of antiarrhythmic or
electrical cardioversion therapy for the first 7 days for treating abnormal
rhythm. A maximum of one event per patient will be considered dichotomously, as
the same event can be reentrant.

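### Excluding patients who have no urine at 48 hours removes severe renal failure from the exploratory NGAL comparison and, if anuria differs between arms, most likely attenuates it

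*Protocol article*

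**What the plan says.** Four parts of the protocol article bear on this.

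- **Sampling.** Data collection lists NGAL in urine at admission and at 48 hours ("48-hour urinary NGAL; presence of surgical site infection in the first 7 days").
- **Definition.** Appendix 1 counts days in the first postoperative week on which the patient was alive "and did not meet the following criteria for renal dysfunction: urinary NGAL", and continues: "value > 150ng/mL. This outcome will be assessed at admission and at 48" hours. The word alive deals with death. Nothing deals with a living patient who produces no urine.
- **Missing data.** Statistical analysis first states that "all randomized patients will be included in the analysis according to the" group assigned. It then says missing data will be managed "with simple exclusion from the analysis". No outcome is exempted.
- **Urine output.** For the creatinine-based definition in Appendix 1, "the diuresis criterion was ignored, as it can be difficult" to interpret after surgery and in cirrhosis. The only urine-output item listed in Data collection is "diuresis in the first 24 hours after surgery", which ends a day before the second NGAL sample.

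Statistical analysis also describes the secondary outcomes, NGAL among them, as exploratory and unadjusted for multiplicity.

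**The concern.** Exclusion is tolerable when samples are lost for reasons unrelated to the patient's kidneys. Here one reason for a missing value is the outcome itself. A patient with no urine at 48 hours has severe renal dysfunction, yet under the stated rule contributes nothing to the renal biomarker comparison.

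The trial's hypothesis is that the higher pressure target protects the kidney. If so, anuria should be more common in the control arm, and exclusion removes more of that arm's worst cases. If the higher target harms the kidney, the same mechanism understates the harm.

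The data items listed also cannot show whether a missing 48-hour sample reflects anuria or a lost tube, so the problem could not be diagnosed afterwards without returning to the charts.

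**Working it through.** **Figure in the plan.** The article gives no rate or power for NGAL, so there is no NGAL figure to reproduce. The sample size supplies the arm size used below. With 73.7% v 53.7%, 80% power, two-sided 5% (sidedness assumed) and unpooled variance, n per arm = (1.960 + 0.842)² × (0.737×0.263 + 0.537×0.463) / 0.20² = 86.8. That is 87 per arm, or 174 in total, as stated.

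**Set-up.** Appendix 1 words the outcome as a count of days over a week, which two samples cannot yield. The check therefore assumes a binary status at 48 hours. For each arm let *a* be the anuric share and *q* the share with NGAL above 150 ng/mL among those with urine. All values of *a* and *q* are assumptions.

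- Every patient classified, anuria counted as dysfunction: t = a + (1 − a)q.
- Anuric patients excluded: q = (t − a)/(1 − a).

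Since t − q = a(1 − q), exclusion lowers the control-minus-intervention difference by a_c(1 − q_c) − a_i(1 − q_i).

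**One case in full.** Anuric 10% v 4% (control v intervention), NGAL-positive 50% v 45%:

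- Control: 0.10 + 0.90×0.50 = 55.0%.
- Intervention: 0.04 + 0.96×0.45 = 47.2%.
- True difference 7.8 points; after exclusion 50 − 45 = 5.0.
- Check: 0.10×0.50 − 0.04×0.55 = 0.028, which is the 2.8 points lost.

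**Range** (control v intervention; a positive difference favours the higher target):

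| Anuric | All classified | Difference | After exclusion | Difference |
|---|---|---|---|---|
| 8% v 4% | 49.4% v 47.2% | 2.2 | 45% v 45% | 0 |
| 10% v 4% | 55.0% v 47.2% | 7.8 | 50% v 45% | 5.0 |
| 5% v 3% | 52.5% v 46.65% | 5.85 | 50% v 45% | 5.0 |
| 10% v 3% | 60% v 50% | 10.0 | 55.6% v 48.5% | 7.1 |
| 10% v 10% | 60% v 50% | 10.0 | 55.6% v 44.4% | 11.1 |
| 15% v 5% | 40% v 35% | 5.0 | 29.4% v 31.6% | −2.2 |

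The first four rows attenuate. With equal anuria nothing is hidden, and the difference grows slightly. The last row reverses, but only by pairing a small true effect with a threefold difference in anuria, and it implies that patients with urine do slightly worse on NGAL under the higher target.

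**Against sampling error.** With 87 per arm at 55.0% v 47.2%, the standard error of the difference is √[(0.55×0.45 + 0.472×0.528)/87] = 7.6 points. The 2.8-point shift is about 0.37 of a standard error. It rests on about 9 v 3 or 4 anuric patients (87×0.10 = 8.7; 87×0.04 = 3.5).

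**The case against.** A fair opponent would say that every rate above is assumed, that bias of any note needs anuria to differ between arms, and that the exclusion criteria (recent renal replacement therapy, treated hepatorenal syndrome, refractory shock, liver-kidney transplants) make anuria less common. The shift is small beside the sampling error. Rules for unobtainable samples often sit in a fuller document. Counting anuria as a positive result also turns a biomarker outcome into a composite. All of this stands as a limit on size. It does not remove the point, because the article goes beyond silence: it fixes a blanket exclusion rule, and for a urine assay that rule selects on the outcome.

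Two stronger readings are tempting, and the documents do not support them.

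- A reader might infer that an anuric patient, having no value above the threshold, did not meet the criterion and so counts as free of dysfunction. In the first row of the table that would give 41.4% v 43.2%, turning a 2.2-point benefit into a 1.8-point apparent harm. But an absent value is missing data, the article has an explicit rule for missing data, and no section says that an unmeasured value counts as a negative one.
- A reader might infer that a kidney benefit or harm could be hidden from the trial as a whole. The primary outcome rests on serum creatinine, and renal replacement therapy and MAKE28 also need no urine sample, so an anuric patient can still be assessed on each of them.

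**Conclusion.** The point holds, and it is minor. The exclusion rule drops living anuric patients from the 48-hour NGAL comparison for a reason tied to the outcome. If anuria differs between arms in the same direction as the true effect, the likely result is attenuation: 0.85 to 2.9 points lost in the four attenuating cases tabulated. Reversal under the stated rule is possible but needs a small effect with a marked anuria imbalance. The sizes rest on assumed anuria and NGAL rates and on reading the outcome as a binary status at 48 hours. Only one comparison is affected, and the article itself says of such "outcomes, and therefore, we suggest that these be interpreted as exploratory" analyses.

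**What to change.** In Appendix 1:

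- State the NGAL outcome as a binary status at 48 hours, replacing the day count.
- Classify a patient who is alive at 48 hours, and from whom no urine can be obtained because of anuria, as meeting NGAL-defined dysfunction. If the concentration is analysed, give that patient the worst rank.

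In Data collection, add one field for the reason each NGAL sample is missing (anuria or logistic), completed from the chart by the external research nurse who already collects the outcomes. In Statistical analysis, limit exclusion for this outcome to samples missing for logistic reasons, and report the complete-case result as a sensitivity analysis.

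The cost is one reworded definition, one field and a chart check for those already enrolled (67.8% of 174, about 118 patients, at the date given under Study perspectives). The rule should be fixed before the data are analysed by arm. No extra patients or tests are needed. The downside is that a few patients are classified without an assay value, so the outcome becomes NGAL above 150 ng/mL or anuria and should be labelled that way.

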### Secondary objective

To evaluate whether higher (85 - 90mmHg) *versus* usual MAP levels
(65 - 70mmHg) in the first 24 hours after liver transplantation surgery are
associated with 28-day mortality; retransplantation in 28 days; renal
replacement therapy in 7 days; surgical site infection within 7 days; days alive
and free of renal dysfunction in 7 days; renal dysfunction according to the
values of neutrophil gelatinase-associated lipocalin (NGAL) at admission and
after 48 hours; length of stay in the ICU; length of hospital stay; days alive
and hospitalization-free in 28 days; liver graft dysfunction (initial poor
function subtype) in 7 days; liver graft dysfunction (primary nonfunction) at 10
days and major adverse kidney events at 28 days (MAKE28).

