### Randomization and blinding

Patients will be randomized within 2 hours of ICU admission after liver
transplantation using a simple 1:1 allocation sequence without group
stratification. The randomization will be performed electronically by the
randomization tool of the Redcap® system. The randomization sequence will
be generated *online* and entered into the system by a staff
member who will not participate in the participant tracking process, in
obtaining informed consent from the patient or in the clinical management of the
cases. The researcher will also not participate in the evaluation of the study
outcome data in order to ensure compliance with the allocation concealment
process.

As the interventions in both groups are based on target MAP levels to be followed
by the professionals involved in the care, the authors chose not to blind the
interventions, which, although possible, would be complex to perform in the
center in question. However, the professional responsible for collecting the
outcome data will be an external research nurse, with no affiliation with the
institution where the study is conducted and who is not involved with the care
offered to each patient. The same care will be taken to hire the statistician
who will analyze the results, ensuring that he or she will not be aware of the
allocated groups. To minimize the risk of bias, an objective primary outcome was
chosen based on test results measured by a certified laboratory.

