### Sample size calculation

Based on the primary outcome incidence of 73.7% (acute renal dysfunction within 7
days) obtained from a database of the same population and location, 174 patients
will be required to demonstrate an absolute reduction of 20% in the primary
outcome, with a power statistic of 80% and alpha of 5%. The data used for this
calculation were obtained by calculating the incidence of AKI based on an
increase in serum creatinine by 1.5 times the baseline value. The criterion used
to choose the effect (20% absolute reduction in the AKI outcome) was chosen
based on the principle of clinical relevance. All patients selected for
transplantation will be evaluated regarding the inclusion and exclusion criteria
and will be informed of the study in a standardized way if able to
participate.

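### The exploratory urinary NGAL outcome is built only on a 150 ng/mL cut although both concentrations are collected; the cut discards information, by an amount that depends on assumptions the protocol does not give

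*Protocol article*

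**What the plan says.** - **Secondary objective** lists renal dysfunction according to the "values of neutrophil gelatinase-associated lipocalin (NGAL) at admission and" after 48 hours, among about a dozen secondary outcomes.
- **Data collection** includes "admission and 48-hour urinary NGAL", so two concentrations per patient are planned.
- **Appendix 1** gives the only working definition. It counts days in the first postoperative week on which the patient was alive and "did not meet the following criteria for renal dysfunction: urinary NGAL value > 150ng/mL", then states that assessment takes place at admission and at 48 hours. A literature reference is attached to the definition, but no reason is given for using the cut as the outcome scale. For creatinine, by contrast, the appendix explains its choice of criterion.
- **Statistical analysis** gives generic rules. Continuous variables go to t or rank tests. For the rest, "Categorical variables will be evaluated using the chi-square test or Fisher’s exact test, as appropriate". No test is assigned to NGAL. Secondary outcomes get effects, 95% confidence intervals and p values without multiplicity adjustment, and are described as exploratory. Missing data are excluded.

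No section makes the NGAL concentration itself an outcome.

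**The concern.** Urinary NGAL is a concentration. Once it is reduced to above or not above 150 ng/mL, a fall from 2,000 to 200 ng/mL counts as no change, while 155 against 145 ng/mL counts as a full event. If most patients in both arms lie on the same side of the cut, a real shift in tubular injury may leave little trace in the result.

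NGAL is the only injury biomarker among the listed outcomes, so it is a useful companion to a primary outcome defined by creatinine. What is at stake is how informative that companion result will be. The primary analysis is not affected.

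The same definition has a second fault. Samples at admission and 48 hours cannot say on which of 7 days the patient was above or below the cut, so the outcome cannot be computed as written. Repairing only this fault, by turning the outcome into a yes/no at 48 hours, would still discard the concentration.

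**Working it through.** **Inputs from the protocol.** 174 patients, a control incidence of 73.7%, "20% absolute reduction in the AKI outcome" and "with a power statistic of 80% and alpha of 5" percent (Sample size calculation); "simple 1:1 allocation sequence" (Randomization and blinding), hence 174/2 = 87 per arm. Sidedness is not stated; I take two-sided.

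**The plan's own figure.** With unpooled variance:

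n = (1.960 + 0.842)² × (0.737×0.263 + 0.537×0.463) / 0.20² = 7.849 × 0.4425 / 0.04 = 86.8, so 87 per arm and 174 in total. The stated size reproduces. It belongs to the creatinine outcome; nothing comparable is given for NGAL.

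**Assumptions for NGAL (mine).** Log NGAL at 48 hours is normal with equal SD in both arms, all 87 per arm are measured, and the cut outcome is read as yes/no at 48 hours. Let p be the control share above 150 ng/mL and d the shift in SD units. The share above the cut in the other arm is then Φ(z(p) − d).

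- Yes/no power = Φ[(|p₁ − p₂| − 1.96·se₀)/se₁], with se₀ pooled and se₁ unpooled.
- Concentration power: two-sample t test, noncentrality d·√(87/2), 172 degrees of freedom.
- ANCOVA on the admission value with correlation r: the same, with d/√(1 − r²) in place of d.

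**Illustration with the primary outcome's contrast placed on the cut.** d = z(0.737) − z(0.537) = 0.634 − 0.093 = 0.541.

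- Yes/no: se₀ = √(2×0.637×0.363/87) = 0.0729 and se₁ = √(0.4425/87) = 0.0713. Power = Φ[(0.200 − 0.1429)/0.0713] = 78.8%.
- t test: noncentrality 0.541 × 6.595 = 3.57; power 94.4%.
- ANCOVA: d becomes 0.567 (r = 0.3) or 0.625 (r = 0.5); power 96.1% or 98.4%.

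Nothing in the protocol links this contrast to NGAL, so it is only one scenario.

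**Range.** Yes/no power in %, with the loss against the t test in points in brackets (losses computed before rounding):

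| Shift (SD) | t test | p = 30% | 50% | 60% | 70% | 90% |
|---|---|---|---|---|---|---|
| 0.1 | 10.1 | 7.1 (2.9) | 7.6 (2.5) | 7.5 (2.5) | 7.3 (2.8) | 5.9 (4.2) |
| 0.2 | 25.9 | 16.2 (9.7) | 18.0 (7.9) | 18.0 (7.9) | 17.2 (8.7) | 12.4 (13.5) |
| 0.3 | 50.3 | 30.2 (20.1) | 34.6 (15.7) | 34.7 (15.6) | 33.3 (17.0) | 23.2 (27.1) |
| 0.4 | 74.6 | 47.3 (27.4) | 54.7 (20.0) | 55.2 (19.4) | 53.6 (21.0) | 38.5 (36.2) |
| 0.54 | 94.4 | 70.5 (23.9) | 79.8 (14.6) | 80.9 (13.5) | 79.9 (14.5) | 63.6 (30.8) |
| 0.8 | 99.9 | 93.8 (6.2) | 98.2 (1.7) | 98.7 (1.2) | 98.7 (1.2) | 94.5 (5.5) |

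For shifts of 0.3 to 0.54 SD the loss is about 14 to 36 points; a finer grid peaks just under 37, at 0.435 SD and p = 90%. At 0.1 and 0.8 SD it is about 1 to 6 points, because both analyses are then weak or both are near full power. A Mann-Whitney test in place of the t test reduces the loss by about 2 points or less. Adjustment for admission NGAL increases it.

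**The case against.** The best defence has five parts.

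1. **The protocol does not specify the yes/no test that the power figures use.** This is correct. Appendix 1 literally defines a day count, and only categorical variables go to chi-square or Fisher. A reader might infer that NGAL is already committed to a chi-square test, but the text does not say so. The figures therefore describe the nearest computable version of the outcome. The information loss remains, because the count is built on the same cut.
2. **The size rests on figures the protocol does not give.** This also stands. A reader might take a loss of 15 to 30 points as a property of this trial, or expect a material loss under any effect. Neither is supported: no NGAL mean, SD, share above the cut or effect is stated, and the loss is small at 0.1 and 0.8 SD.
3. **NGAL's importance can be overstated.** It is tempting to call it the only kidney outcome independent of creatinine. Renal replacement therapy, as defined in Appendix 1, rests on clinical indications without a creatinine threshold, and no section ranks NGAL above the other secondary outcomes.
4. **The outcome is exploratory.** True, and this limits the severity. Effects, intervals and p values are still promised for it, and an estimate on the concentration scale would serve that purpose better.
5. **A 48-hour concentration is undefined after death or without urine, whereas the present wording counts death against the patient.** This stands as a cost of the change, especially as missing data are simply excluded. It has to be handled in the fix.

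**Conclusion.** The point holds, at low severity. The NGAL outcome is defined only through the 150 ng/mL cut, in a day-count form that two samples cannot determine, although both concentrations are collected. Any outcome built on the cut loses information. Under the working's model (normal log NGAL, equal SD, 87 measured per arm, yes/no at 48 hours), the loss is about 14 to 36 points of power for shifts of 0.3 to 0.54 SD with 30% to 90% of controls above the cut, and about 1 to 6 points for shifts of 0.1 or 0.8 SD. This is an assumed range and not a figure derived from trial data. The primary outcome, the 174 patients and the main conclusion do not depend on it.

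**What to change.** - Make the tested NGAL outcome the log-transformed 48-hour urinary concentration, compared between arms by ANCOVA with log admission NGAL as covariate, and report the ratio of geometric means with its 95% CI. Randomization takes place within 2 hours of ICU admission, so the admission value should carry little treatment effect and serves better as a covariate than as an outcome.
- Replace the number-of-days wording in Appendix 1, and keep the proportion above 150 ng/mL at 48 hours as a supporting summary.
- Report by arm how many patients have no 48-hour value because of death or absence of urine. Add a simple sensitivity analysis, such as a rank analysis that places deaths worst.
- Fix the change before anyone sees NGAL results by arm. If that is no longer possible, label the analysis as post hoc.

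**Cost.** Wording only, since both measurements are already planned. A ratio of geometric means is less familiar to clinicians than a percentage, which the supporting summary covers. The main analysis is restricted to patients with a 48-hour sample, hence the sensitivity analysis.

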#### Specific management of the intervention group

The intervention will begin upon admission to the intensive care unit and
will continue for 24 hours after arrival at the ICU. The MAP target of the
intervention group will be 85 - 90mmHg in the first 24 hours after surgery.
The MAP will be measured using an invasive blood pressure catheter, measured
at 1-hour intervals during the first 12 hours and at 2-hour intervals
thereafter until the 24 hours have been completed (according to the protocol
of the ICU). Patients with a MAP lower than the established target may
receive fluids or vasopressors according to the discretion of the attending
physician to achieve the established target MAP.

Noradrenaline will be the initial vasopressor of choice, and the second will
be determined by the attending physician. In hypotensive patients with
reduced cardiac output as monitored by pulmonary artery catheter or
transthoracic echocardiogram, inotropes may be used at the discretion of the
assistant team. Patients who naturally present with a MAP > 90 mmHg even
after complete weaning from vasopressors will not receive additional
vasodilators to reduce the MAP to the study target. The use of vasodilators
in hypertensive patients for the purpose of blood pressure control will be
determined according to the decision of the attending physician.

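### The NGAL outcome is defined as a 7-day count of free days but measured only at admission and 48 hours, so the count cannot be determined and the definition disagrees with the secondary objective

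*Protocol article*

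**What the plan says.** Four parts of the protocol article bear on this outcome.

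- **Appendix 1, item on renal dysfunction by urinary NGAL.** The variable is a day count: "Number of days during the first 7 postoperative days that the patient was alive" and did not meet the criterion, which is a urinary NGAL "value > 150ng/mL". The same item then states "This outcome will be assessed at admission and at 48" hours.
- **Secondary objective.** The outcome is renal dysfunction according to the "values of neutrophil gelatinase-associated lipocalin (NGAL) at admission and" after 48 hours. No day count is mentioned.
- **Data collection.** Urinary NGAL is listed at admission and 48 hours only ("48-hour urinary NGAL; presence of surgical site infection in the first 7 days" is how the list runs on). Creatinine, by contrast, is collected every day: "daily creatinine, to evaluate the presence of acute" kidney failure.
- **Timing.** Under Randomization and blinding: "Patients will be randomized within 2 hours of ICU admission after liver" transplantation. Under Specific management of the intervention group: "The intervention will begin upon admission to the intensive care unit and" lasts 24 hours.

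The Statistical analysis section promises effects, confidence intervals and p values for secondary outcomes, handles missing data by simple exclusion, and asks that secondary outcomes be read as exploratory. It gives no carry-forward or interpolation rule for NGAL.

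**The concern.** A count of free days needs a status for each day. Creatinine has one, so the creatinine-based free-day outcome in the preceding Appendix 1 item can be computed. NGAL does not, so the same form of variable fails here.

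The admission sample raises a second question. It is listed alongside the 48-hour sample as a time at which the outcome is assessed, yet the assigned pressure target has had essentially no time to act by then.

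What is at stake is which analysis is reported. The text leaves room for a threshold at admission, at 48 hours, at either or at both, or for a count filled in by some rule. Unless one is fixed beforehand, the choice will be made once data exist, for a result that carries a p value in an open-label trial.

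**Working it through.** **The plan's own figure.** The only sample size given is 174, for the primary outcome. With 73.7% versus 53.7%, 80% power, two-sided 5% and unpooled variance:

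n per arm = (1.960 + 0.842)² × (0.737 × 0.263 + 0.537 × 0.463) / 0.20² = 7.849 × 0.4425 / 0.04 = 86.8, rounded up to 87, or 174 in total.

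The figure reproduces and has no NGAL input. No power or sample size is stated for NGAL.

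**Inputs for the NGAL count.** Seven days (Appendix 1), two samples (Appendix 1 and Data collection), and a cutoff of 150 ng/mL (Appendix 1). The article does not say how days are numbered, so both readings are shown.

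**Formula.** For a patient alive through day 7, let k be the number of the 7 days with a sample and f the number of those at or below the cutoff. The true count can be any whole number from f to f + (7 − k).

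| Day numbering | k | Days without a value | Samples | Possible count |
|---|---|---|---|---|
| Admission = day 0, 48 h = day 2 | 1 | 6 | 48 h ≤ 150 | 1 to 7 |
| | | | 48 h > 150 | 0 to 6 |
| Admission = day 1, 48 h = day 3 | 2 | 5 | both ≤ 150 | 2 to 7 |
| | | | one > 150 | 1 to 6 |
| | | | both > 150 | 0 to 5 |

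Enumerating every 7-day pattern consistent with the samples gives the same ranges. Even the more generous reading observes 2/7 = 29% of the days, and the ranges for opposite results overlap heavily. If simple exclusion were applied to the unmeasured days, no patient alive through day 7 would have a usable count.

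**Appendix 1 against the Secondary objective.** The objective, taken with the 150 ng/mL cutoff, gives a status at each of two times. The appendix gives a number from 0 to 7. These are different variables under one outcome name.

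**Status of the admission value.** The intervention starts at ICU admission and randomization follows within 2 hours. A sample at admission therefore reflects events up to and during surgery, not the allocated target. This is an inference: the article neither calls the sample a baseline nor says whether it is drawn before randomization.

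**Optional use of the admission value.** If the 48-hour log NGAL is analysed by ANCOVA with admission log NGAL as covariate, the effective sample size is multiplied by 1/(1 − r²), where r is their correlation. The article gives no r, so it is an assumption:

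- r = 0.3: 1/0.91 = 1.10
- r = 0.5: 1/0.75 = 1.33
- r = 0.7: 1/0.51 = 1.96

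**The case against.** The strongest reply is that one sentence is at fault, not the outcome. The heading of the Appendix 1 item and the Secondary objective both describe a status by NGAL at stated times, and with the stated cutoff that can be computed from the planned samples. The day-count sentence nearly repeats the preceding creatinine item, so a drafting slip is plausible, though this too is an inference. This stands in part: NGAL can be analysed under the Secondary objective's wording. It does not rescue the appendix, which the article names as the place where outcomes are defined, and it shows that the two sections must be reconciled.

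A reader might go further and infer that the arms will be tested against each other on the admission value, or that the two times will be pooled and any effect diluted. The article states neither analysis. It provides for paired within-group tests, so the two samples could equally be meant as baseline and follow-up. The supportable criticism is only that admission is listed as an outcome timepoint without its role being fixed.

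It is also fair to say that this is one of about a dozen secondary outcomes, all declared exploratory, and that an ANCOVA is an addition and not a repair.

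**Conclusion.** The concern holds for the definition in Appendix 1. As written, the count cannot be determined for any patient alive through day 7, because 5 or 6 of the 7 days are unobserved depending on day numbering. The definition also disagrees with the Secondary objective. That the admission value is a baseline is a sound inference from the timing, not something the article states.

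A reader might conclude that the NGAL data are unusable or that the trial's main result is threatened. Neither follows. The 48-hour sample supports a clear yes/no outcome, the primary outcome uses creatinine, and 174 does not depend on NGAL. The ANCOVA range of 1.10 to 1.96 rests wholly on an assumed correlation; it describes a possible gain, not the size of the defect. The point should be corrected, but its reach is one exploratory secondary outcome.

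**What to change.** By a dated amendment, made before outcome data by arm are seen:

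1. Delete the day count from the Appendix 1 NGAL item.
2. Word that item and the Secondary objective alike: urinary NGAL above 150 ng/mL at 48 hours, yes or no.
3. Count death before 48 hours as positive, in line with the Main objective's rule for deaths within 7 days, and state this as an exception to simple exclusion of missing data.
4. Remove admission as an outcome timepoint and use admission NGAL as a baseline covariate. State whether the sample is drawn before randomization.
5. Optionally, add a supportive ANCOVA of 48-hour log NGAL adjusted for admission log NGAL.

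The change uses the two samples already planned and needs no further patients. The cost is the amendment itself. Study perspectives reports 67.8% of the sample randomized by 28 February 2023, so the amendment has to be dated and to record that results by arm had not been seen.
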